### 2.2. Hypotheses

According to the literature and the results of other clinical trials, we have elaborated the following hypotheses:

**Hypotheses 1** **(H1)**.*TBCT and MBHP in online modalities are statistically different from PPT online in reducing the symptoms of PTSD*;

**Hypotheses 2** **(H2)**.
*TBCT and MBHP in online modalities are of greater effect size in reducing PTSD symptoms compared to the control (PPT);*

**Hypotheses 3** **(H3)**.*TBCT and MBHP in online modalities contain the largest effect sizes in reducing the symptoms of guilt over the traumatic event compared to the control*;

**Hypotheses 4** **(H4)**.*TBCT and MBHP in online modalities are statistically different from the control, with a larger effect size, in improving quality of life (or disability)*.

### 2.3. Participants

After announcements of the study on the media, interested people seeking online care as a result of COVID-19 will be selected through a self-administered questionnaire, the PTSD Checklist for DSM-5 (PCL-5), which contains a list of PTSD symptoms [47,48,49]. Patients will be contacted by trained evaluators who will use the Structured Clinical Interview for DSM-5 (SCID-5) to ensure the presence of the diagnosis according to DSM-5 criteria. Participants will receive explanations about the study and how psychotherapy works. Those agreeing to participate will sign the informed consent, which includes permission for sessions to be audiotaped. After completion of the self-assessment questionnaires, patients will be randomized to one of the study arms.

### 2.4. Inclusion Criteria

Subjects eligible to participate in this study are adults of both sexes, aged 18 to 60 years old and scoring 45 or more on the PCL-5 as a result of direct or indirect exposure to COVID-19 (e.g., health professionals, people who previously tested positive for COVID-19, or those who quarantined or isolated themselves). Participants should be able to read, write and follow instructions, as well as have access to the Internet.

### 2.5. Exclusion Criteria

Candidates to participate in this study who meet any of the following criteria will be excluded: severe suicide risk (plans, attitudes or suicide attempts during the last 12 months); self-mutilation behavior during the last 12 months; already engaged in another psychotherapy; presenting with psychotic symptoms; and substance use disorder in the last 12 months.

### 2.6. Study Settings

Eligible patients may be located anywhere in the Brazilian territory. The assessors and psychotherapists live in the following Brazilian cities: Nova Iguaçu, Recife, Rio de Janeiro, Salvador São Paulo and Uberlandia. The Federal University of Bahia, in the city of Salvador, is the study headquarters and also home to the principal investigators.

### 2.7. Interventions

The three psychotherapeutic group interventions will be delivered through Skype or Google meeting platforms as weekly, one-hour long sessions, totaling 14 sessions (14 to 17 weeks). The sessions will be audiotaped in order to assure reliability in the fidelity of the intervention and to allow review by qualified supervisors.

Trial-based cognitive therapy

TBCT is a psychotherapeutic intervention whose foundation lies on Beckian CBT [28,50]. Although TBCT, like CBT, includes psychoeducation, cognitive restructuring and behavior experiments assigned as homework, it differs from other CBT approaches in terms of formulation (e.g., TBCT conceptualization diagram), techniques (e.g., participation grid to deal with guilt) and measurement instruments, such as the Cognitive Distortions Questionnaire (CD-Quest) [51] and the Negative Core Beliefs Inventory (NCBI) [52], making TBCT a distinctive approach in restructuring cognition at the three levels of cognition, especially in modifying the dysfunctional negative CBs of patients.

The main TBCT technique, The Trial, was inspired by Kafka’s novel “The Trial” [53]. It was designed to challenge and restructure dysfunctional CBs. A parallel with the CBT perspective is proposed by de Oliveira [54], who argues that the self-accusations presented by the novel’s character, Joseph K., might correspond to the dysfunctional negative CBs about the self. Like Joseph K., patients are not aware of these CBs/self-accusations, but after an investigation by means of the downward arrow approach, the patients become aware of such CBs/self-accusations and learn how to build a proper defense for themselves [54]. The Trial technique includes several CBT components (e.g., examining the evidence) and the empty-chair procedure [55,56], which makes TBCT more experiential [57].

Several studies support the efficacy of TBCT. In the first and preliminary study (*N* = 30) with patients presenting with different diagnoses, this treatment effectively decreased the patients’ attachments to dysfunctional negative CBs, as well as the emotional intensity, during a session [26]. This study [57] was replicated with 166 patients with varying diagnoses and comorbidities, showing a significant reduction in the attachment to dysfunctional CBs and in emotional intensity.

It has also been demonstrated in a randomized clinical trial (*N* = 36) comparing TBCT techniques to conventional CBT techniques that TBCT was as efficacious as conventional CBT techniques in reducing social anxiety symptoms and improving quality of life and more efficacious than CBT in reducing fear of negative evaluation, social avoidance and distress [31,34]. A second study aiming to evaluate the efficacy of TBCT for generalized social anxiety disorder in a population with high rates of comorbid disorders, especially depression [33], was carried out. This was a two-arm randomized clinical trial that included 39 adults (TBCT = 18; waitlist group = 21), and symptom severity was assessed at pre- and post-treatment. Reductions in social anxiety, social avoidance and depression were observed in the participants in the TBCT group, of which all were associated with a large effect size, while no differences between pre- and post-treatment scores were observed in the waitlist condition. Interestingly, patients with comorbid conditions showed greater reductions in social anxiety symptoms across treatment relative to those with SAD only.

A study (*N* = 76) comparing the efficacy of TBCT, behavioral activation (BA) and treatment as usual (TAU) in the treatment of major depressive disorder [30] showed that both TBCT and BA (which also included antidepressants) were different from TAU (which included antidepressants alone) in reducing the HAM-D and BDI scores.

Recently, 95 patients who met DSM-4-TR criteria for PTSD were randomly assigned to receive either TBCT or prolonged exposure (PE) [25]. A significant reduction in the primary outcome as assessed by the Davidson Trauma Scale (DTS) was improvement in PTSD symptoms. Reductions in DTS scores were observed in both arms, but there was no significant difference between treatments. Regarding the secondary outcomes (depression, anxiety and dysfunctional attitudes assessed by the Beck Depression/Anxiety Inventories and Dysfunctional Attitudes Scale, as well as the dropout rate), significant differences in depressive symptoms were observed in favor of TBCT. In addition, the dropout rate was lower in the TBCT group than in the PE group, suggesting that TBCT may be an effective alternative for treating PTSD.

Mindfulness-based health promotion

“*Mindfulness-Based Health Promotion (MBHP)”* is the *Mindfulness* program protocol adopted by the Mente Aberta Center and has therefore become the basis of its professional training. MBHP was inspired by Jon Kabat-Zinn’s original model, *Mindfulness-Based Stress Reduction*, adapted to the context of Health and Quality of Life Promotion. Besides mindfulness-based stress reduction (MBSB), other inspirations have contributed to the MBHP protocol, including *Mindfulness-Based Cognitive Therapy* (MBCT) and *Mindfulness-Based Relapse Prevention*, both programs used by British Institutes [58,59].

The MBHP program was designed for the Brazilian and Hispanic-American context and in terms of its applicability in public policies in the areas of health, education and organizations. Potential beneficiaries of MBHP are public health care system professionals and patients (particularly those with chronic transdiagnostic conditions), public school students and teachers, police officers and other public workers, as well as the population at large. Evidence on the MBHP protocol has accumulated over the last decade, showing its efficacy and effectiveness in improving health-related quality of life, anxiety, depression and burnout symptoms; in particular through mechanisms such as decentering and self-compassion [36,37,38]. There are no studies specifically on PTSD symptoms, and this project addresses this gap. On the other hand, other mindfulness protocols have been shown to be effective for PTSD, especially those inspired by MBHP, such as the MBSR and MBCT [58,59].

Just as is the case with the classical *Mindfulness* approaches (MBSR and MBCT), the purpose of MBHP is to develop “Awareness” through the practice of *Mindfulness* (which involves attention, attitude and intention). Awareness is understood as being conscious (*aware*) of (realizing, acknowledging, perceiving, noticing and observing) inner phenomena (thoughts, feelings, emotions, sensations and impulses) and external phenomena (activities, relations, etc.). The assumption (principle/intention) is that, if the person is aware, he/she is more likely to make more assertive/conscious decisions/choices, responding to situations in a less reactive way (no more acting on “auto-pilot”). There is scientific evidence showing that developing *Awareness* is one of the basic mechanisms that explain the benefits of *Mindfulness* in health promotion, bringing self-efficacy and quality of life.

The definition of *Mindfulness* we use is that provided by *Jon Kabat-Zinn himself*: “*Mindfulness* is awareness that arises through paying attention, on purpose, in the present moment, non-judgmentally and non-critically, to the experience that emerges moment-by-moment.”

The original MBHP protocol is a structured program developed over eight sessions, in groups, where participants (8–15 people) meet every week for 2 h (standard duration of one session) to experience the concepts and techniques of mindfulness. However, MBHP was designed so it would allow customization when applied to public policies. If necessary, the number and duration of sessions may be changed, so it can be flexible and dynamic in its use by organizations, schools and health care services. Furthermore, to match the conditions of the present study, the protocol will be individual, 1 h sessions, delivered over 14 encounters (14 sessions).

Participants are also given suggestions of daily activities to be implemented at home or in the workplace, which last on average 15–20 min, but may last up to 45 min in the case of more motivated and compliant participants. They are also encouraged to incorporate the idea of *Mindfulness* in their daily lives (the so-called “informal practice”), so all daily activities somehow become opportunities to practice Mindfulness.

Positive psychotherapy

PPT is the clinical and therapeutic arm of positive psychology (PP). After empirical validation, PPT was organized in a cohesive protocol of 15 sessions. Many of the practices of PPT have been studied through online interventions. In the present study, the protocol will be reduced to 14 sessions, which is in agreement with the other arms of this clinical trial. PPT integrates symptoms with strengths, risks with resources, weaknesses with values and regrets with hopes, aiming to understand the inherent complexities of human experience in a balanced way. Without ignoring or minimizing the client’s concerns, the PPT clinician empathetically understands and pays attention to the pain associated with the trauma and simultaneously explores the potential for growth. PPT considers that clients in psychological distress can be better understood and served if they learn to use their highest resources—personal and interpersonal—to face the challenges in life [39,43,44,60].

PPT is divided into three phases. In phase 1, the patient creates a personal narrative, remembering and writing a story that awakened his/her best, especially in overcoming a challenge (a strategy called positive presentation). In subsequent sessions, which correspond to most of the therapeutic work in this phase, it focuses on the assessment and organization of a profile of the signature strengths and the acquisition of the skills necessary to integrate the forces with psychological stressors [44].

In phase 2, after establishing therapeutic rapport and helping clients identify their strengths, clinicians encourage them to write about their grudges, bitter memories or resentments and then discuss the effects of holding on to these negative aspects. PPT does not discourage the expression of negative expressions; it encourages clients to evaluate a wide range of emotions, positive and negative [44].

Phase 3 focuses on restoring or encouraging positive relationships. At this point, patients are likely to be ready to seek meaning and purpose; the forces have broadened the self-concepts of clients, and they are able to deal with disturbing memories, learn about forgiveness and begin to see the benefits of gratitude. Phase 3 also encourages patients to cultivate meaning through engaging in a number of processes, such as strengthening intimate and community personal relationships; the search for artistic, intellectual or scientific innovations; or engaging in philosophical or religious contemplation [44].

In his book “Flourishing”, Martin Seligman describes some programs applied in the US Army based on positive psychology. The results appeared to be promising, despite initial concerns [45]. However, other more detailed studies with a more rigid scientific design seem to be necessary. In any case, it is important to understand that the main focus of interventions based on positive psychology is not directly reducing symptoms of illness, that is, PTSD, but investing in aspects related to resilience, in this case, post-traumatic growth (PTG). PTG is defined as positive, meaningful psychological changes that an individual can experience as a result of coping with traumatic life events [61,62]. A review of nine qualitative studies with military and former military personnel showed that PTG is a phenomenon that can also occur after exposure to trauma in wars [46,62].

### 2.8. Outcomes

Primary outcomes will be assessed by the reduction in PTSD symptoms, measured through CAPS-5. Secondary outcomes will be the improvement in symptoms of anxiety, depression and well-being. Mediator variables will also be assessed, measuring negative CBs, guilt and the strength of the therapeutic alliance. All scales will be applied by a blind assessor to the intervention groups before randomization (Initial Assessment), after seven sessions (Intermediate Assessment) and after 14 sessions (Final Assessment). They will also be applied in the 3-, 6- and 12-month follow-ups. Table 1 shows the flow of sessions and evaluations over the study period. Table 1 shows the SPIRIT diagram.

### 2.9. Instruments

Diagnostic assessment

Structural Clinical Interview for the DSM-5 (SCID-5) [63]: It is a semi-structured psychiatric interview, with the purpose of providing a diagnosis, according to the Diagnostic and Statistical Manual of Mental Disorders (DSM-5).

*PCL-5 PTSD Check List 5:* It contains 20 items with the purpose of assessing PTSD symptoms, in accordance with criteria B, C, D and E (DSM-5). Each item is scored on a scale that ranges from 0 (not at all) to 4 (extremely) [47,48,49]. This scale will be applied only at intake.

Primary outcome

Clinician-Administered PTSD Scale (CAPS-5) [64]: It is a diagnostic interview scale with 30 items to assess the diagnosis and severity of PTSD symptoms in accordance with DSM-5 [65,66]. CAPS-5 will be applied at baseline, mid-treatment (session seven) and post-treatment (session fourteen), as well as at follow-up (3, 6 and 12 months).

Secondary outcome

*Hospital Anxiety and Depression Scale* (HADS) [65]: This is a 14-item scale used to determine anxiety and depression symptoms, where each item is worth 0 to 3 points, and a total score of 9 or higher suggests mild symptoms. It was translated and validated for the Brazilian population [67,68]. This scale will be administered at baseline (initial evaluation), mid-treatment (week 7) and post-treatment (week 14), as well as at 3-, 6- and 12-month follow-ups.

*The World Health Organization Five Well-Being Index (WHO-5):* This is an overall well-being scale, with five questions and scores ranging from 0 to 5, addressing mood and energy [69,70]. The WHO-5 validation study into Brazilian Portuguese included 1128 individuals. During this research, the instrument presented good internal validity (Cronbach’s alpha = 0.83) [71]. WHO-5 will be applied at baseline, mid-treatment (session seven) and post-treatment (session 14), as well as at the follow-ups (3, 6 and 12 months).

Mediator variables

Trauma-Related Guilt Inventory (TRGI) [72]: This is a 32-item questionnaire assessing the cognitive and emotional aspects of guilt that are associated to a specific traumatic event. TRGI will be applied at baseline, mid-treatment (session 7) and post-treatment (session 14), as well as at the follow-ups (3, 6 and 12 months).

Negative Core Beliefs Inventory (NCBI) [52]: This inventory is designed to assess negative CBs, as described by [73]. It consists of 50 items evaluating beliefs about oneself and the world, on a Likert scale of 1 to 4 points each. NCBI will be applied at baseline, mid-treatment (session seven) and post-treatment (session 14), as well as at the follow-ups (3, 6 and 12 months).

*California Psychotherapeutic Alliance Scale—patient version (CALPAS-P):* Scale that assesses four dimensions of the therapeutic relationship [74,75]: (1) therapeutic alliance, (2) working alliance, (3) understanding and (4) therapist involvement, based on an agreement between patient and therapist about the goals of therapy. The CALPAS-P has 24 items ranging from 1 (never) to 7 (always) on the Likert scale. This scale will be administered at the end of second, fourth, sixth, eighth, tenth, twelfth and fourteenth psychotherapy sessions.

### 2.10. Sample Size

The sample size calculation was estimated using the G*Power software version 3.1 [76], considering a mixed design. Parameters that were taken into account were the F test and repeated measures ANOVA for comparison between groups, for an effect size of 0.25, α criterion of 0.05 and power of (1−β) 0.80, three groups design (TBCT X MBHP X WBT), three measures (baseline, mid-treatment and final assessment), and an a priori correlation between the repeated measures of 0.50. Hence, a sample of 108 participants was obtained, with a numerator of 2 and a denominator of 105 degrees of freedom, for a critical F of 3.08. Considering a 25% dropout rate, a total of 135 participants was estimated.

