### 2.15. Statistical Methods

The collected data will be analyzed statistically using the Statistics Package for Social Science software (SPSS), version 24.0 [77]. Clinical and demographic categorical variables will be analyzed with *X*^2^ (sex, education, color or race, and dropout rate) and continuous variables will be assessed with one-way ANOVA (age and scale scores). Missing data for both primary and secondary outcome measures will be analyzed by intention to treat (ITT) and multiple imputation (IM), with five imputed databases taking baseline and sociodemographic data and assuming the random chance mechanism. Generalized estimation equations (GHG), taking time as a covariate, will be performed to compare changes in scores over time and between groups (TCP, MBSR and PP). Effect sizes will be evaluated according to Cohen’s tests. The assumed level of statistical significance will be 0.05.

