## 3. Discussion

To the best of our knowledge, this is the first study at the international level to compare the effects of three different psychosocial interventions on PTSD symptons. Moreover, the current pandemic caused by the dissemination of the COVID-19 virus has caused worry and unprecedented impacts on mortality rates, on the economy and on mental health. The impact on the latter, however, has been very well established, as anxiety and depression symptoms, including suicidal behavior, have increased significantly in the general population as a result of the pandemic [78]. Symptoms are directly influenced by alarming, excessive and unreliable news; by the risks of contamination; by the risks of it affecting the individual’s own life or that of their loved ones; and by restriction on activities and financial losses. Long periods of uncertainty, insecurity and feelings of inefficacy bring about anguish and anxiety, as they are considered predictors of trauma. Studies suggest that individuals who are close to the most vulnerable patients tend to be more affected than health professionals on the frontline [78], because although the health care context involves higher risks, it also has more control measures against contamination. In any case, the general population is more vulnerable to stress- and trauma-related disorders, especially PTSD [79,80]. This is clearly a stress-related disorder with well-defined triggering cognitive models [81].

To date, psychotherapy is the first treatment option for PTSD, as it restructures trauma-related cognitions, thus reducing symptoms that impact quality of life, such as reactions of anxiety, stress and insomnia. In our study, from a randomized and controlled design, integrating quantitative and qualitative measures, and with a sample with good statistical power, we innovated by testing and comparing two new interventions that proved effective for mental disorders, mindfulness and positive psychology, which has the potential to bring relevant new clinical information to the international literature.

Qualitative data will be collected on how patients and psychotherapists see the pandemic as a whole and online therapies. Although data on the impact of the pandemic on health professionals have already been published [79], there are no qualitative studies addressing online psychotherapy during the pandemic.

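### The 80% power in section 2.10 is for a group main effect averaged over visits that include baseline, not for the between-group comparison of change in CAPS-5 that the trial plans

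*Protocol article*

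**What the plan says.** Section 2.10 (Sample Size) describes a G*Power calculation using "the F test and repeated measures ANOVA for comparison between groups, for an effect size of 0.25", alpha 0.05, power 0.80, three groups, "three measures (baseline, mid-treatment and final assessment" visits, and a correlation of 0.50 between repeated measures. It reports 108 participants "with a numerator of 2 and a denominator of 105 degrees of freedom" and a critical F of 3.08, then raises the total to 135 for 25% dropout.

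Section 2.8 (Outcomes) defines the primary outcome as the reduction in PTSD symptoms on CAPS-5 and places the initial assessment before randomisation. Section 2.15 (Statistical Methods) plans generalised estimating equations with time as a covariate, which "will be performed to compare changes in scores over time and between groups". The Discussion describes the study as one "with a sample with good statistical power".

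**The concern.** The degrees of freedom 2 and 105 are k − 1 and N − k for three groups and 108 patients. They belong to the between-subjects main effect of group, a test that averages each patient's three scores and compares those averages across arms. In a repeated-measures ANOVA with three categorical visits, the group-by-time test would have 4 and 210.

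One of the three averaged scores is taken before randomisation. Its expected difference between arms is zero, so it dilutes whatever effect exists later. The trial's question, in H1, the primary outcome and section 2.15, is whether scores fall by different amounts in the three arms. The power statement therefore belongs to a contrast that the question does not use.

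The consequence is mainly one of interpretation. The Abstract expects no statistical difference among the three therapies. If that is what is found, the stated 80% power and the Discussion's wording invite readers to take a null result as good evidence of similarity. The calculation as written does not support that.

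**Working it through.** **Inputs from section 2.10.** k = 3 groups, m = 3 visits, f = 0.25, ρ = 0.50, α = 0.05, N = 108, df 2 and 105, critical F 3.08, 25% dropout, 135 in total.

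**1. Reproduce the plan's figure.** For the between-groups main effect, λ = f²·N·m / [1 + (m − 1)ρ] with df (2, N − 3).
- The factor m / [1 + (m − 1)ρ] is 3/2 = 1.5.
- N = 105: λ = 0.0625 × 105 × 1.5 = 9.84, power 0.797.
- N = 108: λ = 0.0625 × 108 × 1.5 = 10.13, critical F(2, 105) = 3.083, power 0.809.

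So 108 is the smallest multiple of three that reaches 0.80, and the published figure is reproduced. The software's within-between interaction option with the same inputs gives N = 36, and the within-factor option gives N = 30. Only the main-effect option gives 108 with df 2 and 105. The 36 does not show that the trial is oversized, because f is defined differently there: an end-of-treatment f of 0.25 corresponds to an interaction f of only about 0.10 to 0.12.

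**2. What an averaged f of 0.25 means with equal baselines.** The protocol gives no time course, so two patterns are assumed.
- Full effect from mid-treatment: average = (0 + 1 + 1)/3 = 2/3 of the final effect, so the final f must be 0.25 / (2/3) = 0.375.
- Linear growth: average = (0 + 0.5 + 1)/3 = 1/2 of the final effect, so the final f must be 0.25 / 0.5 = 0.50.

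**3. Power if f = 0.25 is the effect at the final assessment (an assumption), ρ = 0.50.** The lower N is 135 × 0.75 = 101, which applies if 25% are lost and contribute nothing.
- Change from baseline: λ = N·f² / [2(1 − ρ)] = N·f², df (2, N − 3).
- Final score adjusted for baseline: λ = N·f² / (1 − ρ²) = N·f² / 0.75, df (2, N − 4).

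| Comparison | λ at 108 | Power at 108 | λ at 101 | Power at 101 | f for 80% at 108 (101) |
|---|---|---|---|---|---|
| Change from baseline | 6.75 | 0.63 | 6.31 | 0.59 | 0.30 (0.31) |
| Final score adjusted for baseline | 9.00 | 0.76 | 8.42 | 0.73 | 0.26 (0.27) |

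At this effect, 80% power would need 159 evaluable patients for change and 120 for the adjusted final score. The 4-df group-by-time test at N = 108 has power 0.51 under linear growth and 0.65 with the full effect from mid-treatment.

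**4. Power if 0.25 is the averaged effect.** The final f is then 0.375 to 0.50. Change-score power is 0.94 (λ = 108 × 0.375² = 15.19) to above 0.99 (λ = 108 × 0.50² = 27.0) at 108. At 101 it is 0.92 to above 0.99.

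**5. Dependence on the correlation.** The formulas in step 3, with f = 0.25 and N = 108, give for change 0.48 at ρ = 0.3 and 0.85 at ρ = 0.7. For the adjusted final score they give 0.67 and 0.90. The protocol's own value is 0.50.

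**The case against.** The strongest reply is that no shortfall has been shown. The formula fixes only the difference averaged over visits. That average is compatible with arms that are equal at baseline and differ by f = 0.375 to 0.50 at the end, in which case 108 patients are ample for a comparison of change. This stands. A reader might infer that the calculation assumes arms already different at baseline, or that the trial is underpowered. The documents support neither: the first holds only if 0.25 is read as the effect at every visit, and the second only if 0.25 is read as the end-of-treatment effect. Section 2.10 says neither.

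A second reply is that section 2.15 takes time as a covariate, so a linear group-by-time term would have 2 numerator degrees of freedom rather than 4, and the text does not say which coefficient is tested. This also stands, and it is why the comparison with 4 and 210 is confined to categorical time. It does not rescue the match. The denominator of 105 and the exact reproduction of 108 still identify a test on averaged scores, whereas section 2.15 compares changes.

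Third, the figures at 101 treat dropouts as contributing nothing, although section 2.15 plans intention to treat with multiple imputation. They are a lower scenario. The conclusion does not depend on them, since at ρ = 0.50 and f = 0.25 both comparisons are already below 0.80 at 108.

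**Conclusion.** Section 2.10 is wrong as written: its 80% power is for the main effect of group averaged over visits that include a pre-randomisation baseline, and it does not carry over to the planned comparison of change. This rests on the protocol's own degrees of freedom and on the exact reproduction of N = 108.

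The size of any shortfall is conditional on what 0.25 was meant to be. If it is the end-of-treatment effect, power falls short by about 0.17 for change (0.80 − 0.63) and about 0.04 for the adjusted final score (0.80 − 0.76), at 108 evaluable and ρ = 0.50. A correlation of 0.7 would remove the shortfall. If 0.25 is the averaged effect, power is well above 0.80, but the trial then relies on an end-of-treatment f of 0.375 to 0.50 between three active therapies, which the protocol neither states nor justifies. Either way the reader cannot tell what difference in CAPS-5 the trial can detect.

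**What to change.** In section 2.10:
- Drop baseline from the measures that carry the treatment effect.
- State the target effect on the between-group contrast in CAPS-5 at the final assessment.
- Restate power, or the detectable effect, for 135 randomised under the model in section 2.15.

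With ρ = 0.50, the end-of-treatment f detectable with 80% power is about 0.30 at 108 evaluable (0.31 at 101) for a comparison of change. It is 0.26 (0.27) if the final score is adjusted for baseline CAPS-5. Section 2.15 does not currently plan that adjustment, so the second pair may be quoted only if section 2.15 is amended to include it. The power wording in the Discussion should be brought into line with the restated figure.

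The cost is rewording, one line in section 2.15 if baseline adjustment is adopted, and a stated power that may be less favourable. No extra patients are required.
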